## Background

Survival from childhood and adolescent cancer has increased significantly in the past several decades, from under 50% in the 1970s to over 80% today [1]. This remarkable achievement has resulted in an exponential increase in the number of childhood cancer survivors living in the United States, projected to exceed 500,000 by this year [2]. However, the price of cure includes a significant burden of treatment-related morbidities. Seventy percent of adult survivors are estimated to suffer from one or more severe, disabling, or life-threatening chronic health conditions (CHC) or 'late effects' that significantly and negatively impact their quality of life [3, 4]. Down syndrome (DS) is a genetic disorder that results from a constitutional trisomy of chromosome 21. This disorder is associated with distinguishing phenotypic features, intellectual disability, co-occurring structural birth defects, and an increased risk for CHC. Children with DS are also at increased risk for developing hematologic malignancies, with a 10 to 20-fold excess risk in comparison with the general population, so that between 1:100 and 1:150 children with DS will develop acute leukemia (AL), [5, 6] predominantly B-lineage acute lymphoblastic leukemia (ALL) or acute myeloid leukemia (AML), composing 2% of all pediatric ALL cases and 15% of all pediatric AML cases. During treatment for AL, children with DS experience excess acute cancer therapy-related toxicities compared to their non-DS peers with ALL and AML [7–9].

In the absence of DS, AL treatment confers a substantial risk for late effects. Among 272 AML survivors enrolled to the Childhood Cancer Survivor Study (CCSS), the cumulative incidence of CHC at 20 years from diagnosis was 50%, of which 16% were severe, compared with only 6% of sibling controls [10]. Similarly, at 25 years from diagnosis, the cumulative incidence of CHC among ALL survivors enrolled to CCSS was 65%, of which 21% were graded as severe [11]. A meta-analysis of neurocognitive sequelae of childhood ALL provides consistent evidence that cancer therapy impacts intellectual function even in the absence of radiation exposure, particularly with respect to attention, working memory, and processing speed [12, 13], although less is known regarding the neurocognitive sequelae of AML treatment [14].

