### Recruitment, population, and eligibility

A unique feature of this observational survivorship trial is the hybrid recruitment approach that leverages the COG Childhood Cancer Research Network (ACCRN07) and Project EveryChild (APEC14B1) research registration and biobanking protocols [33, 34]. Potential participants with DS-AL are identified and recruited by two mechanisms run in parallel: 1) The Coordinating Center conducts centralized recruitment of patients that have consented to recontact and were enrolled to either ACCRN07, APEC14B1, and/or AEPI20N2 The DS-ALL Deep Phenotyping Project: Evaluating the Association Between Co-occurring Birth defects and ALL Risk in DS; 2) Site-based prospective recruitment at COG sites that have activated the study protocol (only for subjects not enrolled to any of the above registries or studies).

Eligible survivors are those with DS-AL who are ≥ 6 years old and < 40 years old, in remission, at least 36 months off primary cancer treatment, and able to understand either English or Spanish. Bone marrow transplant recipients are excluded (see Table 2). A diagnosis of Down syndrome is required and may include any of the three recognized types: trisomy 21 resulting from chromosomal nondisjunction (most common), translocation (the patient has 46 chromosomes, but all or part of an additional copy of chromosome 21 is attached to another chromosome), or mosaicism (trisomy 21 that is present in only a fraction of cells). All participants to ALTE22C1 must be a survivor of either ALL or AML/myeloid leukemia of DS (ML-DS) requiring treatment with chemotherapy and may not have had any other cancer diagnosis other than transient abnormal myelopoiesis. Based on the racial and ethnic distribution of childhood leukemia in the United States, the sample is expected to be 70% White, 10% Black, 20% other or multi-race, and about 20% Hispanic (estimates derived from the Surveillance Epidemiology and End Results Program).

**Table 2 Tab2:** Eligibility Criteria for COG ALTE22C1

Inclusion Criteria
• Age ≥ 6 and < 40 years at the time of enrollment
• Diagnosis of Down syndrome
• Survivor of ALL or AML treated with chemotherapy for their cancer diagnosis
• Completed treatment at least 36 calendar months prior to enrollment
• Life expectance > 1 year
• English or Spanish speaking
Exclusion Criteria
• History of hematopoietic stem cell transplant
• History of another cancer either prior to or subsequent to the ALL/AML diagnosis

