### Statistical analyses

For Part 1 data, the prevalence for each CHC will be estimated and compared with published CHC prevalence and grading data from non-DS AL survivor cohorts using CTCAE criteria [10, 11, 43, 44]. We will then construct longitudinal data to power time-to-event analyses, using two modeling approaches [45] to account for time-varying independent variable (diagnosis with AL) effects on time to a dependent variable (CHC incidence and CHC-free survival). Subjects without a CHC event will be censored at the time of study enrollment (DS-AL) or update of CHC or neurocognitive data (DS controls). For all analyses, we will pool observations over equal length intervals of chronologic age to predict short term risk of CHC during each age interval. First, we will use pooled logistic regression to estimate OR, 95% CI, and p-values for association of ALL, AML, or any AL diagnosis with medical record-verified CHC, agnostic of time to CHC. Next, we will use stratified Cox models to refine associations of ALL, AML, or any AL diagnosis with CHC based on time to CHC incidence. Within each age interval, we will estimate the hazard ratios (HR), 95% CI, and p-values to report time-dependent effects of ALL, AML, or any AL diagnosis on CHC. All models will be adjusted for age, sex, race/ethnicity, and relevant cancer or DS characteristics.

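### The CHC censoring rule lets an event-free control be followed to a neurocognitive update, which can add unobserved CHC-free time and push the leukemia hazard ratio upward

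*Protocol article*

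**What the plan says.** The section on statistical analyses sets the end of follow-up for the CHC models: "Subjects without a CHC event will be censored at the time of study enrollment (DS-AL) or update of CHC or neurocognitive data (DS controls"). The outcome is "time to a dependent variable (CHC incidence and CHC-free survival"), and the time axis is age: "we will pool observations over equal length intervals of chronologic age to predict short term risk of CHC during each age interval". The Cox step reads: "Next, we will use stratified Cox models to refine associations of ALL, AML, or any AL diagnosis with CHC based on time to CHC incidence".

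The section on data collection says that controls receive the same CHC measures as survivors and also the same neurocognitive battery, and that their CHC, with onset dates, are verified by record review. It does not say whether the two kinds of data are updated on the same date. Nor does the article say which date governs when they differ.

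**The concern.** The rule applies to people with no CHC event, so its date should be the last date on which an event could have been seen. A parent-rated neurocognitive score is not such a date. If it is the later one, the control contributes time at risk with no possibility of an event.

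The neurocognitive alternative has no other use in this rule. Part 1 neurocognitive scores are compared between survivors and controls by t-test (or a nonparametric alternative) and by proportions. The Cox models for neurocognitive deficits, under Part 3, use predictors such as age at leukemia diagnosis, years off therapy and treatment exposures, so they concern survivors only. Controls enter no neurocognitive time-to-event analysis, and the clause therefore acts only on their CHC follow-up.

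The rule gives survivors no such extension. Any excess falls on the control side and moves the primary HR in the direction that the study hypothesizes.

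**Working it through.** **Inputs from the article.** Baseline hazard 0.062 (time unit not stated, taken as per year), 200 vs 200 for ALL and 100 vs 100 for AML, two-sided alpha 0.05 (section on sample size and power). Survivor age 6 to under 40 (eligibility).

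**Assumptions, not in the article.** The gap g between last CHC ascertainment and the credited censoring date; the length of follow-up; a constant hazard; leukemia status treated as fixed rather than time-varying, for simplicity.

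**The plan's own figure.** The plan gives no figure for this bias. The nearest yardstick is its detectable HR for ALL, 0.084/0.062 = 1.355. By Schoenfeld's formula this needs 4(1.960 + 0.842)²/(ln 1.355)² ≈ 341 events among 400 people. The article states neither follow-up nor event fraction, so the 80% power can be neither confirmed nor refuted. It is used here only for scale.

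**Step 1, closed form.** With hazard h and CHC ascertained for T years, a control has expected events 1 − exp(−hT) and expected true time at risk [1 − exp(−hT)]/h. Crediting g further years to those still event-free adds g·exp(−hT). With a true HR of 1, the apparent HR is

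1 + g·h·exp(−hT)/[1 − exp(−hT)].

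For h = 0.062 and T = 18, exp(−1.116) = 0.328, so the term per year of gap is 0.062 × 0.328/0.672 = 0.030.

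| T (years) | g = 1 | g = 2 | g = 3 |
|---|---|---|---|
| 10 | 1.07 | 1.14 | 1.22 |
| 18 | 1.03 | 1.06 | 1.09 |
| 20 | 1.03 | 1.05 | 1.08 |

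**Step 2, Cox simulation on the age scale.** True HR 1, censoring age uniform on 6 to 40, control ascertainment ending g years before the credited age, 2,000 runs per setting. Each cell gives the mean HR (averaged on the log scale) and the type I error.

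| Setting | g = 0 | g = 1 | g = 2 | g = 3 | g = 5 |
|---|---|---|---|---|---|
| 200 vs 200, h = 0.062 | 1.00, 5.4% | 1.03, 5.4% | 1.05, 7.0% | 1.10, 10.6% | 1.19, 28.6% |
| 100 vs 100, h = 0.062 | 1.00, 5.0% | 1.03, 6.0% | 1.06, 6.0% | 1.09, 7.8% | 1.20, 18.2% |
| 200 vs 200, h = 0.02 (assumed, rarer CHC) | 1.00, 6.2% | 1.03, 5.5% | 1.08, 7.8% | 1.13, 9.8% | 1.25, 22.9% |
| 200 vs 200, h = 0.062, half of controls affected | – | – | 1.03, 5.4% | – | 1.10, 12.7% |

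The Monte Carlo standard error near 5% is √(0.05 × 0.95/2000) ≈ 0.5 percentage points, so a 1-year gap cannot be told apart from no gap on type I error.

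**Step 3, is it the gap or the unequal end dates?** With controls followed 5 years longer than survivors but CHC ascertained throughout, the HR is 1.00 and the type I error 5.7%. Only the unascertained time causes bias.

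**The case against.** The strongest reply is that nothing in the article says the two updates ever differ in date. The data-collection section is compatible with collecting CHC and neurocognitive data together. Record review with onset dates may also carry CHC ascertainment past the survey date. An article may leave exact censoring dates to the full protocol. Small gaps do little harm, and gaps of about 3 years or more across all controls are documented nowhere. All of this stands, and it makes the bias conditional and modest. It does not remove the point, because the rule as printed names a date that carries no CHC information.

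Three stronger readings are tempting, and the article does not support them.

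- **Unequal stopping points as a bias in themselves.** A reader might object that survivors stop at enrollment and controls at an update. On an age scale with non-informative censoring this gives no bias (step 3).
- **A mislabelled hazard ratio.** Survivors must be alive to enroll ("Completed treatment at least 36 calendar months prior to enrollment"), and the article does not mention death as an event, so a reader might say that the survival endpoint is misnamed. But the Cox HR is tied to time to CHC incidence, the endpoint name can be read as remaining free of CHC, and the declared population is survivors.
- **Acute toxicity passing as a late effect.** Exposure starts at leukemia diagnosis, and the background says: "During treatment for AL, children with DS experience excess acute cancer therapy-related toxicities compared to their non-DS peers". A reader might infer that treatment-period onset contaminates the HR. The exposure is openly defined that way, the primary aim does not limit onset to the period after treatment, and the discussion places both acute and late-onset toxicity in scope. Splitting exposure by treatment phase is a preference and not a correction.

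**Conclusion.** The point holds as a conditional flaw in a stated rule. Read literally, the rule can credit controls with time in which CHC were not ascertained, and that moves the leukemia HR upward from a true value of 1. At the plan's hazard, with every control affected, the inflation is about 1.03 to 1.10 for gaps of 1 to 3 years, with type I error rising from about 5% to about 11% in the 200 vs 200 comparison. On the log scale a 3-year gap is roughly 0.3 of the plan's detectable effect (ln 1.10/ln 1.355 = 0.31). It is about half as large at 2 years if half the controls are affected, and larger if CHC follow-up is short or the condition rarer. These sizes rest on assumed gaps and follow-up, since the article gives no update dates. If CHC and neurocognitive data are always updated together, the bias is zero and only the wording needs repair. Severity is minor to moderate.

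**What to change.** Remove the neurocognitive alternative from the CHC censoring rule. Censor every event-free subject, survivor or control, at the date CHC status was last ascertained by survey or record review, and count events only up to that same date. If the control cohort always refreshes both data types together, say so.

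The cost is a wording change, plus use of each subject's CHC ascertainment date. No new data collection or change in sample size follows. In the simulation, censoring at last CHC ascertainment (g = 0) returns the HR to 1.00 and type I error to about 5%. A post-treatment HR may be added as an optional sensitivity analysis, but this point does not require it.

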### Sample size and power calculations

In a pilot study, we observed a higher likelihood of acquired cataracts among DS-AL survivors compared to DS controls, possibly related to steroid exposure during leukemia treatment (p-value = 0.03, all cases were DS-ALL survivors treated with steroids), and a higher likelihood of any cardiovascular or cerebrovascular event among DS-AL survivors compared to DS controls, possibly related to anthracycline exposure during leukemia treatment (p-value = 0.01, all cases were anthracycline-exposed). Based on these differences, with a sample size of 200 DS-ALL survivors and 200 DS controls, we will have 80% power to detect a hazard of 0.046 or 0.084, assuming a 2-sided alpha of 0.05 and an exponential baseline hazard of 0.062. With a sample size of 100 DS-AML survivors and 100 DS controls under the same assumptions, we will have 80% power to detect a hazard of 0.040 or 0.096. Based on the findings of Roncadin et al., [39] we will have 90% power to detect a 10-point difference in mean score for adaptive behavior. Assuming an expected standard deviation (SD) of 20 based on published data using the PedsQL to assess quality of life in populations with intellectual disabilities in comparison to those without disabilities [40], we will have 80% power to detect a difference in the mean scores of at least 4 to 6 points between DS-AL survivors and DS controls, sufficient to permit differentiation of healthy from acute or chronically ill subjects [41].

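### Time-dependent leukemia effects are to be reported from a separate HR and p-value in each age interval, with no stated comparison of the HRs, so a constant effect can readily be misread as age-specific

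*Protocol article*

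**What the plan says.** In the protocol article, Statistical analyses, the Part 1 CHC analysis is built on age intervals: "we will pool observations over equal length intervals of chronologic age to predict short term risk of CHC during each age interval". Pooled logistic regression comes first, then stratified Cox models for ALL, AML or any acute leukemia (AL). The section then states how dependence on time will be presented: "Within each age interval, we will estimate the hazard ratios (HR), 95% CI, and p-values to report time-dependent effects" of each leukemia grouping on CHC. Neither the number nor the length of the intervals is given.

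The section Sample size and power calculations gives power for one overall hazard contrast per leukemia type. For ALL, "with a sample size of 200 DS-ALL survivors and 200 DS controls", it says "we will have 80% power to detect a hazard of 0.046 or 0.084". The control hazard is taken as constant at 0.062, and the test is two-sided at 0.05. For AML it says "With a sample size of 100 DS-AML survivors and 100 DS controls under the same assumptions, we will have 80% power"; the hazards there are 0.040 or 0.096. No power is given, or claimed, for a single age interval.

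No part of the article mentions a leukemia-by-age interaction, a heterogeneity test across intervals, or a test of a time-varying coefficient.

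**The concern.** To say that an effect depends on time is to say that the HR differs between ages. An interval p-value addresses something else: whether the HR differs from 1 at those ages. One significant interval next to a non-significant one is quite compatible with the same HR in both, particularly when each holds only a share of the events. A list of interval HRs with p-values therefore cannot by itself support the conclusion it is meant to report.

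The analysis serves the primary aim, the comparison of CHC between survivors and controls. The Discussion expects evidence of excess risk to support added surveillance. An age band wrongly read as the only one with excess risk, or as free of it, could be carried into that use.

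**Working it through.** **Inputs from the article (Sample size and power calculations).** Two-sided alpha 0.05; control hazard 0.062; 1:1 groups; 80% power at hazard 0.084 or 0.046 (ALL, 200 per group) and at 0.096 or 0.040 (AML, 100 per group). The detectable HRs are 0.084/0.062 = 1.355 and 0.046/0.062 = 0.742 for ALL, and 0.096/0.062 = 1.548 and 0.040/0.062 = 0.645 for AML.

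**Assumptions, not in the article.** K = 2 to 8 intervals, a constant HR, and intervals that are approximately independent. The main calculation also divides events equally between intervals.

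**Step 1: the stated 80%.** By Schoenfeld's formula, events = 4(1.960 + 0.842)² / (ln HR)².

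- ALL: 341 events for HR 1.355 or 353 for HR 0.742, out of 400 people (85% to 88%).
- AML: 165 events for HR 1.548 or 164 for HR 0.645, out of 200 people (82% to 83%).

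The article gives no event count or follow-up time, so the 80% cannot be reproduced outright. It fits the stated inputs only if about 82% to 88% of people have an event. The next steps take the 80% as given.

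**Step 2: power in one interval.** The overall noncentrality is 1.960 + 0.842 = 2.802. With equal events, each interval has 2.802/√K. For K = 4 this is 1.401, and power p = P(Z > 1.960 − 1.401) = P(Z > 0.559) = 29%; the opposite tail is negligible.

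**Step 3: the pattern across intervals.** P(some significant, others not) = 1 − p^K − (1 − p)^K. With no effect, P(at least one significant) = 1 − 0.95^K.

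| K | Power per interval | Some significant, others not | All significant | None significant | No effect: at least one significant |
|---|---|---|---|---|---|
| 2 | 51% | 50% | 26% | 24% | 9.8% |
| 3 | 37% | 70% | 4.9% | 25% | 14.3% |
| 4 | 29% | 74% | 0.7% | 26% | 18.5% |
| 5 | 24% | 75% | 0.1% | 25% | 22.6% |
| 8 | 17% | 77% | about 0% | 23% | 33.7% |

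The ALL and AML designs give the same percentages to within rounding, because both start from 80% overall power.

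**Step 4: sensitivity to overall power.**

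- At 50% overall power, the mixed pattern occurs in 41% (K=2), 49% (K=3) and 51% (K=4).
- At 90%, it occurs in 47%, 75% and 82%.
- For an outcome with one fifth of the events and K = 4, the interval noncentrality is 2.802 × √(0.2/4) = 0.627. Two-sided power is then 9.6%, and the mixed pattern occurs in 1 − 0.096⁴ − 0.904⁴ = 33%.

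**Step 5: check by simulation.** The ALL design was run 3000 times for each K with control hazard 0.062, constant HR 1.355, censoring age uniform from 6 to 40, and equal-length intervals on 0 to 40. Leukemia exposure was simplified to be present from age 0. Events then fall unequally between intervals. The mixed pattern occurred in 66%, 72% and 74% of runs for K = 2, 3 and 4. One heterogeneity test on K − 1 degrees of freedom wrongly called the effect age-dependent in 4.4%, 4.3% and 5.3% of the same runs. At larger K, and for AML from K = 3, near-empty late intervals distorted this simple test, so those rates are not used.

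**The case against.** **No decision rule is stated.** The article does not say that age-dependence will be judged by comparing p-values, and it reports estimates and CIs alongside them. This stands. A reader might infer that the authors have committed themselves to the error, and the text does not go that far. It does name a purpose and the means to it, and those means include no comparison of the HRs.

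**Time-dependent may refer to the exposure.** The same section treats leukemia diagnosis as a time-varying variable, so the phrase could mean the effect of a time-dependent exposure. That explains how the covariate is coded. It does not explain why a separate HR and p-value is wanted in each age interval.

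**The test may be in an analysis plan that is not shown.** An interaction test is commonly left to such a plan, and its absence alone would be no finding. The point here is that the method the article does state cannot carry the conclusion attached to it.

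**Overall estimates may already exist.** The pooled logistic and Cox models may well give an overall effect, so part of the remedy may already be met. An overall HR still does not compare the intervals. The power section claims nothing about intervals, so there is no error in it on this point.

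**The size depends on assumptions.** This also stands. K is unknown, and the 80% anchor needs a very high event proportion. The primary outcome is broken down by category, organ system and grade, so many individual outcomes will have far fewer events.

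**Conclusion.** The concern holds in a limited form. Interval-by-interval HRs and p-values are the stated means of reporting time-dependent effects, and they do not test whether the effect changes with age. With a constant HR at 80% overall power and equal events, a mixed pattern of significance arises in 50% (K=2) to 75% (K=5) of studies. With no effect, 10% to 23% of studies show at least one significant interval, for each outcome and leukemia grouping. A constant effect can therefore readily be misread as age-specific.

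Two stronger readings are not supported:

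- **That a constant effect will usually look age-specific.** This needs three or more intervals and an effect near the design value. It is an even chance at K = 2 with equal events, 41% to 51% at 50% overall power (K = 2 to 4), and about 33% at K = 4 with one fifth of the events. Equal-length intervals with enrollment up to age 40 make three or more intervals plausible, but the article does not say so. A mixed pattern also misleads only if it is read as age-dependence.
- **That the study is meant to set the ages at which survivors need surveillance.** The Aims do not say this, and the Discussion speaks of added surveillance without reference to age bands.

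**What to change.** Replace the sentence on interval-specific HRs with wording such as: Whether the leukemia effect on CHC changes with age will be judged by one likelihood-ratio test of the leukemia-by-age-interval interaction, or by a time-varying coefficient in the Cox model. The overall HR is the inferential result. Interval-specific HRs will be shown with 95% CIs as description only.

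The intervals should be fixed in advance and be wide enough to hold events in both groups, since near-empty intervals distorted the heterogeneity test in the simulation.

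The change costs one model term and a few sentences, and needs no new data. The study is still enrolling, so it can be made before analysis. The downside is that a single age interval can no longer be claimed as significant on its own. The interaction test also has modest power, so a non-significant result must not be read as showing a constant effect.

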• Parent or guardian unable to complete the required forms

The comparison population (‘DS controls’) are active participants in an ongoing research study cohort of children and young adults with DS. Recruitment to this study began in 1989 as a population-based case–control study conducted in the five-county metropolitan area of Atlanta and has since expanded recruitment to sites across the United States. Recruitment and enrollment methods to this study are described previously [35–38]. Controls will be frequency-matched to cases by age, sex, and, when possible, race and ethnicity.

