For Part 1 neurocognitive data, we will determine both raw and standardized scores derived from age-based norms for all tests. Quantitative data will be summarized with descriptive statistics and correlational techniques. Given inherent challenges of interpreting age-normalized results in an intellectually disabled population, data will be evaluated for evidence of floor effects, i.e., an atypical left-shifted distribution of standard scores for measures where lower scores suggest lower skill ratings (Vineland, CCC-2) or a rightward shift for measures where higher scores indicate more behavioral issues (BRIEF-2, SCQ, NCBRF). Mean scores for each assessment will be compared between DS-AL survivors and DS controls, as well as between DS-AL subgroups and DS controls. The mean score for each test will be compared between the cohorts using a Student t-test (2-sided significance level of 0.05 and equal variance). If atypical score distributions restrict our ability to use parametric statistics, we will consider nonparametric approaches to group comparisons or score transformations to facilitate use of parametric modeling. In addition, we will utilize frequency comparisons, with scores dichotomized as clinically significant impairment yes/no according to manualized procedures (≤ 1.5 SD outside of the mean for the age-normative sample) and will compare the proportion of subjects ‘at the floor’ between DS-AL survivors, DS-AL subgroups, and DS controls.

For Part 2, the proportion of results that are ‘abnormal’ for each test will be detailed using descriptive statistics and compared between DS-ALL and DS-AML survivors.

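### Survivor-control neurocognitive scores are compared by an unadjusted t-test, although controls are only frequency-matched and the chronic-condition models for the same groups are covariate-adjusted

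*Protocol article*

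**What the plan says.** Four statements in the protocol article bear on this point.

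- **Comparisons** (Statistical analyses, Part 1 neurocognitive data): "Mean scores for each assessment will be compared between DS-AL survivors and DS controls, as well as between DS-AL subgroups and DS controls".
- **Test** (same paragraph): "The mean score for each test will be compared between the cohorts using a Student t-test (2-sided significance level of 0.05 and equal variance". No covariates are named. The only fallback concerns atypical score distributions, in which case "we will consider nonparametric approaches to group comparisons or score transformations to facilitate use of parametric modeling".
- **Matching** (Recruitment, population, and eligibility): "Controls will be frequency-matched to cases by age, sex, and, when possible, race and ethnicity".
- **Adjustment elsewhere** (Statistical analyses, end of the CHC regression paragraph): "All models will be adjusted for age, sex, race/ethnicity, and relevant cancer or DS characteristics".

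On age, the plan says "we will determine both raw and standardized scores derived from age-based norms for all tests", and follows with a caution: "Given inherent challenges of interpreting age-normalized results in an intellectually disabled population, data will be evaluated for evidence of floor effects".

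**The concern.** Survivors come from Children's Oncology Group registries and sites. Controls come from a separate cohort that began in metropolitan Atlanta and later expanded. Without randomization, comparability rests on the matching and on the analysis.

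Frequency matching aligns the distributions of the matching factors only in the group for which it is done, and only as well as the available controls allow. The article concedes that race and ethnicity may not be matched. It does not say whether age and sex are matched separately within ALL and AML, yet each subgroup is compared with controls. A t-test cannot correct what the matching leaves over.

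At stake is a stated secondary aim: parent-reported neurocognitive outcomes in survivors against people with Down syndrome and no leukemia. A leftover difference in age or race/ethnicity would appear as an effect of leukemia or its treatment, or would hide one.

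**Working it through.** **1. Does the adjustment sentence cover this analysis?** It closes the paragraph on pooled logistic and Cox models for CHC. The neurocognitive paragraph comes after it and names a t-test, which has no covariates. The Part 3 paragraph describes further adjusted models, but those relate risk factors, variants and telomere length to outcomes among survivors; they are not the survivor-control comparison. So the mean-score comparison is unadjusted as written.

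**2. Group sizes, checked on the plan's own figure.** Sample size and power calculations pairs 200 DS-ALL with 200 controls and 100 DS-AML with 100 controls. It also states 80% power for a PedsQL difference of 4 to 6 points at SD 20, without giving n. The detectable difference is (1.960 + 0.842) × 20 × √(1/n₁ + 1/n₂):

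- 300 vs 300: 4.57 points
- 200 vs 200: 5.60 points
- 100 vs 100: 7.92 points

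The pooled and ALL values fall inside the stated range. The figure is not in dispute here; it only supports working with 1:1 sizes.

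**3. Type I error when age is not balanced.** Let r be the correlation of score with age within groups and d the age gap in SDs of age. With no true group effect, the spurious difference is r × d score SDs. With k = r·d / √(1/n₁ + 1/n₂), the chance of a significant result is Φ(−1.96 + k) + Φ(−1.96 − k).

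Example: r = 0.3, d = 0.25, 100 vs 100. Here k = 0.075 / 0.1414 = 0.53, so the type I error is 8.3%. At d = 0.5, k = 1.06 and it is 18.6%.

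| r | d | 100 vs 100 | 200 vs 200 |
|---|---|---|---|
| 0.2 | 0.25 | 6.4% | 7.9% |
| 0.2 | 0.5 | 10.9% | 17.0% |
| 0.3 | 0.25 | 8.3% | 11.7% |
| 0.3 | 0.5 | 18.6% | 32.3% |
| 0.5 | 0.25 | 14.3% | 24.0% |
| 0.5 | 0.5 | 42.4% | 70.5% |

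The documents give neither r nor d; both are assumptions. For scale, if ages were spread evenly from 6 to 40 (also an assumption), the age SD would be 34/√12 = 9.8 years, so the two gaps would be about 2.5 and 4.9 years.

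**4. Does adjustment repair it?** Simulation at 100 vs 100 with r = 0.3 (4,000 runs per case):

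| Test | d = 0.25 | d = 0.5 |
|---|---|---|
| Student t-test | 8.5% | 17.9% |
| Welch test | 8.5% | 17.9% |
| Regression on group and age | 4.4% | 4.7% |

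Over all sizes and gaps tried, the age-adjusted analysis stayed at about 4-6%. Allowing unequal variances does not help; the covariate does.

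**5. If matching is perfect.** With age exactly balanced, the t-test still counts age-related variation as noise. Its true size is 2 × [1 − Φ(1.96/√(1 − r²))]: 4.6% at r = 0.2, 4.0% at r = 0.3 and 2.4% at r = 0.5. Adjustment would shrink the standard error by the factor √(1 − r²), which is 0.954 at r = 0.3 and 0.866 at r = 0.5.

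**6. Equal variance.** The true size of the pooled test is 2 × [1 − Φ(1.96 × √(pooled variance / true variance))], both being variances of the mean difference. With n₁ = n₂ they coincide, so the size stays at 5.0% for SD ratios from 0.67 to 1.5. With sizes that the article does not give, such as 100 vs 300, it would run from 1.7% to 10.7% over that range.

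**The case against.** The other side has several fair points.

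- **Age is not ignored.** It is a matching factor, and age-normed scores and impairment classifications are used beside raw scores. This stands in part: it lowers the risk from age, most of all in the pooled comparison. But the article itself doubts age-normed results in this population, raw scores are also determined, and age norms do nothing for race/ethnicity.
- **Imbalance is a risk, not a fact.** This stands. Matching within subgroups is neither stated nor excluded, and no age distributions are given.
- **The analysis plan may add adjustment.** This does not answer the point: the article names the test, so it is a stated choice and not a detail left open.

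A reader might infer stronger claims that the documents do not support.

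- **One shared control set that distorts the error rates.** The analysis section says only DS controls, while the sample size section gives separate control counts for ALL and AML. Even with 300 shared controls, simulation leaves each comparison at 5.0%.
- **An invalid pooled-variance test.** It keeps its size at the planned 1:1 allocation. It can mislead only if group sizes and SDs both differ.
- **A bias as large as the detectable PedsQL difference.** Reaching 6 points at SD 20 takes, for example, an assumed drift of 1 SD per 10 years and an age gap of 3 years (0.3 × 20 = 6). Neither is in the documents, and the SD of 20 belongs to quality of life, for which no such age slope is given.

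**Conclusion.** The point holds as a weakness in a stated analysis of a secondary aim. The article fixes an unadjusted comparison for non-randomized groups whose matching it describes as partial, and it departs from its own adjusted approach to the CHC outcomes. The exposure is greatest for race/ethnicity, for ALL and AML against controls, and for raw scores; it is smallest for age-normed scores in the pooled comparison.

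The size depends on quantities that the article does not give. At 100 vs 100, an age-score correlation of 0.2 to 0.5 and a gap of 0.25 to 0.5 SD put the type I error between 6.4% and 42.4%; the central case (correlation 0.3) gives about 8.5% or 18%. With exact balance it falls below 5% and precision is lost. Adjustment is the better choice in either case. No figure is offered for race/ethnicity, because the documents give nothing to base one on. The equal-variance assumption is a minor matter at the planned sizes.

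**What to change.** Make the main comparison of each score a linear regression on group, with age at completion of the battery, sex and race/ethnicity as covariates and heteroscedasticity-robust standard errors. Use it for all AL, for ALL and for AML against controls. Allow a curved age effect for raw scores, since ages run from 6 to 39. Keep the t-test as a descriptive summary, and keep the existing check for floor effects with its fallback.

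The cost is a change of wording. The covariates are already matching factors and CHC-model covariates, so no new data are needed. Robust standard errors also remove the reliance on equal variances if the final group sizes turn out unequal. Recruitment was still under way in August 2025, with 112 participants in Part 1, so the change can be fixed before the comparison is run.
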